### Sham Acupuncture Interventions

The optimal control group for studies of acupuncture is controversial. Sham acupuncture methods include acupuncture for an unrelated condition, needle insertion at nonacupoint locations, noninsertive simulated acupuncture, or use of retractable needles. However, most acupuncture controls are not completely inert. Potential benefits may be conferred from the physiologic effect of needling even when not performed according to established principles. (131-134) Detrimental effects from sham needling are also possible, and other studies have found no benefit in the sham group. (134)

In the prior sham-controlled study of acupuncture for AI-related joint symptoms, the sham intervention used superficial needle insertion at body locations not recognized as true acupoints. (80) Results showed that 22% of subjects who received sham acupuncture reported at least a 2-point decrease in BPI-SF worst pain scores, consistent with the literature that reports a 25-55% placebo effect for nonacupoint and superficial insertion sham methods. (135) In this study, 57% of patients in the sham group believed they were receiving true acupuncture, suggesting that blinding was effective. For the auricular acupuncture, the sham intervention will involve adding adhesives to the selected points on the helix of the auricle. While a sham auricular intervention was not applied in the prior study, investigators feel that application of the sham auricular intervention may increase the effectiveness of blinding. While future studies may attempt to look at other point protocols and acupuncture interventions oriented in other traditional theories, investigators feel that it is important to remain consistent in this study design. Moreover, investigators will control for a placebo effect based on previous research as reflected in the statistical methods.

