7.3 Follow-Up Visits

a. Follow-up visits will occur at 6 and 12 weeks after registration.

Acupuncture adherence will be ascertained by the Columbia CRA by maintenance of the acupuncturist-completed web-based study calendar and documentation on the **S1200** Adherence to Acupuncture Form (Form #6044). Adverse events will be assessed and recorded on the **S1200** Adverse Event Summary Form (Form #5183). Use of pain medications will be recorded on the **S1200** Supplemental Agents Reporting Form (Form #9413). At 6 weeks and 12 weeks, to assess the adequacy of blinding, patients in the true and sham acupuncture groups will give an opinion about their treatment assignment. All of this data will be recorded on the **S1200** Assessment of Blinding (Form #20574).

Patients will be instructed to complete the following self-administered questionnaires. It takes about 30 minutes to complete the assessments. **See Section 15.2 for instructions for administration of the questionnaires.**

- **S1200** Brief Pain Inventory-Short Form (BPI-SF) (Form #40963)
- **S1200** Western Ontario and McMaster Universities Osteoarthritis (WOMAC) Index (Version 3.1) (Form #33579)
- **S1200** Modified-Score for the Assessment and Quantification of Chronic Rheumatoid Affections of the Hands (M-SACRAH) (Form #48347)
- **S1200** PROMIS Pain Impact-Short Form (PROMIS PI-SF) (Form #28494)
- **S1200** FACT-ES Outcome Trial Outcome Index (Version 4) (Form #13659)
- **S1200** Aromatase Inhibitor Usage Form (Form #39879)

The nurse or CRA will also complete the **S1200** Cover Sheet for Patient-Completed Questionnaires (Form #19445).

Functional testing (grip strength, 'Timed Get Up and Go') will be conducted and recorded on the **S1200** Functional testing (Form #37709). **See Section 7.5 for instructions for functional testing.**

Additionally, blood will be drawn for serum hormones (estradiol, FSH, LH) and inflammatory markers (TNF $\alpha$ , IL-6, IL-12, CRP) (see Section 15.2). Urine will be collected for urine CTX-II.

- b. Follow-up visits after the 12-week study intervention will occur at 24 and 52 weeks after registration.

Patients will be instructed to complete the same self-administered questionnaires as listed in Section 7.3a.

The nurse or CRA will also complete the **S1200** Cover Sheet for Patient-Completed Questionnaires (Form #19445).

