For a 2-point difference and a 3.0 point SD at 6 weeks, with other parameters as specified above, 208 total eligible patients (104 true acupuncture, 52 sham acupuncture, and 52 waitlist control) would be required for 82% power for the two comparisons, based on two separate t-tests. [Note that in power calculations, the combination of the 5% non-adherence rate and the 10% contamination rate, stipulated above, reduces the nominal effect size of a 2 point difference to 1.7 points; while the 10% dropout rate inflates the estimated sample size by a factor of 1/0.9 or about 11%.] This approach allows two fully-powered independent comparisons between true acupuncture and the two alternatives. In addition, unlike an ANOVA approach, it does not assume equal variances across the three arms, which may be more appropriate in this setting given the inclusion of a waitlist control. Power will be higher with lower observed standard deviation.

A multiple linear regression analysis of the primary endpoint will include the baseline score as well as the pre-specified stratification factor. To allow for an ineligibility of 8% (based on a recent study, [S0715](#)), a total of 228 patients will be enrolled to achieve 208 eligible patients.

The potential for different dropout by arm, especially with respect to the waitlist control, will be mitigated by monthly conferences among study investigators to encourage proper assessment and submission of forms at every required timepoint for all patients. Dropout patterns will be monitored on an ongoing basis.

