#### 11.2 Secondary endpoints:

- a. Secondary hypotheses (Section 10.2) will include assessment of intervention differences at each timepoint individually (weeks 6, 12, 16, 20, 24, and 52), as well as longitudinal modeling of the outcome measures over time. For longitudinal modeling, linear mixed models will be used; if there is evidence of non-random dropout, pattern-mixture models will be utilized as sensitivity analysis. Covariates for longitudinal modeling will include intervention assignment, assessment time, their interaction, baseline score, and other potential confounding variables (*i.e.* age).
- b. Exploratory analyses will also be done to evaluate the relationship between aromatase gene polymorphisms (*CYP19A1*) and inflammatory biomarkers with severity of joint symptoms and response to acupuncture treatment.
- c. A further exploratory analysis at both 6 and 12 weeks according to adherence to intervention assignment will be conducted, with receipt of  $\geq 80\%$  of planned treatment sessions defined as “adherent.” (In particular, patients will be divided into the adherent true ( $\geq 80\%$ ), non-adherent true ( $< 80\%$ ), adherent sham ( $\geq 80\%$ ), and non-adherent sham ( $< 80\%$ ) acupuncture groups.) The interaction between treatment adherence category and treatment category will be tested. Adherence to acupuncture sessions as a continuous measure will also be evaluated.
- d. The success of blinding will be evaluated by using chi-square tests to compare the percentage of patients in each group who believed that they had received true acupuncture at Weeks 6, 12, 24, and 52.

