### Comments:

[figure not shown]

**DRAFT****SWOG  
S1200 ASSESSMENT OF BLINDING**

Page 1 of 1

SWOG Patient ID  SWOG Study No. S1200 Registration Step 1

Patient Initials \_\_\_\_\_ (L, F M)

Date of Completion:  /  / **Planned assessment:** ☐ 6-week visit ☐ 12-week visit ☐ 24-week visit ☐ 52-week visit**Instructions:** You will be asked to complete this form at 6 weeks, 12 weeks, 24 weeks and 52 weeks post-registration. Thank you for your participation on this study.**1. Do you think you were receiving true acupuncture during your study participation?**☐ Yes ☐ No ☐ Not applicable (Waitlist control arm)**2. Did you get any acupuncture treatments outside of this clinical study?**☐ Yes ☐ No**If Yes, how many acupuncture treatments did you receive in the past 6 months outside of this clinical study?** [figure not shown]

**DRAFT****SWOG  
S1200 OFF PROTOCOL NOTICE**

Page 1 of 1

SWOG Patient ID 

SWOG Study No. S1200

Registration Step 1

Patient Initials \_\_\_\_\_ (L, F M)

Institution / Affiliate \_\_\_\_\_ Physician \_\_\_\_\_

**Instructions:** Submit this form within 2 weeks after completion (or discontinuation) of study intervention.All dates are **MONTH, DAY, YEAR**. Explain any blank fields or blank dates in the **Comments** section.Place an ☒ in appropriate boxes.**Off Protocol Reason** (select one):

- ☐ Completion of 12 weeks of study intervention
- ☐ Medically required, specify: \_\_\_\_\_
- ☐ Patient refused, logistics (e.g., transportation) or scheduling conflicts, specify: \_\_\_\_\_
- ☐ Patient refused, other reason, specify: \_\_\_\_\_
- ☐ Evidence of any cancer, specify: \_\_\_\_\_
- ☐ Death (submit Notice of Death form)
- ☐ Other, specify: \_\_\_\_\_

**Off Protocol Date**Date of completion, evidence of cancer, death or decision to discontinue therapy:  /  / Date of Last Contact or Death:  /  / Vital Status: ☐ Alive ☐ Dead (submit Notice of Death form)**Comments:**[figure not shown]

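### The yes/no blinding item cannot separate belief from guessing, so similar Yes percentages in the true and sham arms would be weak evidence that blinding worked

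*Protocol*

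**What the plan says.** Protocol Section 11.2d fixes the blinding analysis. Success is judged by chi-square tests, and their stated task is this: "compare the percentage of patients in each group who believed that they had received true acupuncture at Weeks 6, 12, 24, and 52".

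The answers come from item 1 of Form #20574 in Section 18.0, which asks: "Do you think you were receiving true acupuncture during your study participation". The boxes that follow run "Yes ☐ No ☐ Not applicable (Waitlist control arm". The third box is labelled for the waitlist arm, so a needled woman chooses between Yes and No or leaves the item unanswered. Section 7.3 describes the data only as an opinion: "patients in the true and sham acupuncture groups will give an opinion about their treatment assignment".

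No section offers a box for being unsure or a rating of certainty.

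The background in Section 2.0 shows how such a percentage is likely to be read. Of the earlier sham-controlled trial it says that "57% of patients in the sham group believed they were receiving true acupuncture, suggesting that blinding was effective".

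**The concern.** The plan's statistic is described as belief, but the form cannot tell a woman who holds a view from one who has none and ticks a box because she was asked. Under a good blind many women may have no view. Their guessed Yes answers go into the numerator as belief, and their guessed No answers count as disbelief. A blank does not help, because it does not say that she was unsure.

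The primary endpoint is a self-reported pain score, so the true-versus-sham contrast leans on the blind. The two procedures also feel different: Section 19.1 has needling to a *de qi* sensation and ear needles in the true arm, and shallow needling with ear adhesives in the sham arm. The blinding check is what a reader will turn to when judging whether expectation could explain a difference. Certainty that is never asked for cannot be recovered by any later analysis plan.

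**Working it through.** **Inputs from the protocol.** Section 11.1 gives 104 true and 52 sham eligible patients and 10% dropout at 6 weeks, hence 104 × 0.9 = 93.6 and 52 × 0.9 = 46.8 respondents. The 57% sham belief rate comes from the earlier trial in Section 2.0.

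**The plan's own figure.** The protocol states no power for the blinding test. Its primary power serves to confirm the arm sizes: "208 total eligible patients (104 true acupuncture, 52 sham acupuncture, and 52 waitlist control) would be required for 82% power". With a 1.7-point difference, SD 3.0 and two-sided α of 0.025, the standard error is 3.0 × √(1/93.6 + 1/46.8) = 0.537, and 1.7/0.537 = 3.165. Power is Φ(3.165 − 2.241) = 82%. The figure is reproduced.

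**Assumptions not in the documents.** Among women with a view, 77% in the true arm believe they had true acupuncture. The sham value of 57% is borrowed from the earlier trial. Undecided women tick Yes at rate g. The blinding test is two-sided at 5%.

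**Model.** Let b be the share believing *true* among women with a view, and u the undecided share. Then observed Yes = (1 − u)b + ug.

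**Case 1: u and g equal in both arms.** The guesses cancel and the gap is (1 − u)(b_true − b_sham). With g = 0.5:

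| u | Yes, true | Yes, sham | Gap | Power of the planned test |
|---|---|---|---|---|
| 0 | 77.0% | 57.0% | 20 | 68% |
| 0.2 | 71.6% | 55.6% | 16 | 47% |
| 0.4 | 66.2% | 54.2% | 12 | 28% |

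Power is Φ[(gap − 1.96·SE₀)/SE₁], with SE₀ pooled and SE₁ unpooled. For u = 0.2 this is Φ[(0.160 − 1.96 × 0.0846)/0.0863] = 47%.

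**Case 2: u differs by arm, g = 0.3.**

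- u_true = 0.1, u_sham = 0.4: 0.9 × 0.77 + 0.03 = 72.3%, against 0.6 × 0.57 + 0.12 = 46.2%. The gap is 26 points, larger than 20.
- u_true = 0.4, u_sham = 0.1: 0.6 × 0.77 + 0.12 = 58.2%, against 0.9 × 0.57 + 0.03 = 54.3%. The gap is 4 points.

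**Case 3: no difference in belief.** Take b = 0.80 in both arms, u_true = 0.1 and u_sham = 0.4. With g = 0.3 the rates are 75% and 60%, a gap of 15 points. With g = 0.7 they are 79% and 76%, a gap of 3 points. The whole gap comes from unequal undecided shares and from guessing.

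**Would an extra box alone help?** No. If an unsure category were added but Section 11.2d still took Yes as a percentage of all women, the Case 1 gaps would be 0.8 × 20 = 16 and 0.6 × 20 = 12 points, as before. A three-category chi-square test has power of about 49% and 38% at u = 0.2 and 0.4, against 47% and 28% for the forced item. At u = 0.1 it has 54% against 58%. The gain is mainly in what can be described.

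**What can be described.** Take an index equal to the share guessing their arm correctly minus the share guessing wrongly, among all respondents, with unsure counted as neither. At u = 0.4 in Case 1 it is 0.462 − 0.138 = 0.32 in the true arm and 0.258 − 0.342 = −0.08 in the sham arm. The yes/no item cannot supply these quantities.

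**The case against.** The strongest defence is that a forced choice is a legitimate design. It draws out weak suspicion that an unsure box lets people avoid, and it gives a percentage of the same kind as the one quoted for the earlier trial. Section 11.2d and the form agree with each other, the planned test compares two arms rather than reading the sham rate alone, and this is a supporting check. An analysis confined to women with a view would also select on a response given after randomisation, which pain relief itself may influence. All of this stands. It is a reason to keep the yes/no question and not to rest on a test among opinion-holders. It does not remove the gap in the data: the form never records whether a Yes was held or guessed.

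A reader might go further and infer that the item always dilutes a real difference, so that unblinding is bound to look smaller than it is. The documents do not support that. Dilution needs equal undecided shares and equal guessing rates in both arms, and nothing in the protocol establishes either. Even with belief as far apart as an assumed 80% and 45%, undecided shares of 10% and 40% with g = 0.3 give 0.72 + 0.03 = 75% against 0.27 + 0.12 = 39%, a gap of 36 points where the true one is 35.

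Nor can the 57% in the earlier sham arm be taken as proof of guessing. The protocol does not say which item that trial used or how many of its patients were undecided.

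**Conclusion.** The point holds in a limited form. The percentage in Section 11.2d mixes belief with guessing, so similar Yes percentages in the two needled arms are weak evidence of successful blinding, and a difference between them is not clean evidence of failure. With equal undecided shares and guessing rates the gap among women with a view shrinks by the factor (1 − u). With unequal undecided shares it can shrink, grow or arise from guesses alone.

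The figures above are illustrations. The undecided shares, the guessing rates and the 77%, 80% and 45% belief rates are assumptions, and applying the earlier trial's 57% to women with a view is a further one. Size and direction in this trial are unknown. The primary endpoint, its significance level, the sample size and the primary analysis are untouched. This is a cheap improvement to a supporting check.

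**What to change.** Keep the yes/no question on Form #20574 and add one line beneath it for the true and sham arms: *How sure are you? not at all / somewhat / very*. Class *not at all* as unsure.

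In Section 11.2d, state that Yes, No and unsure will be reported by arm among all true and sham respondents at each time point, with an arm-specific blinding index and its confidence interval. Keep the chi-square test on the forced answer alongside, which preserves comparability with the earlier trial. Do not rest the conclusion on a test restricted to women who express a view.

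The cost is one extra tick-box at each of four visits, a slight added burden for patients, and a sentence or two in Section 11.2d. The copy of the form in Section 18.0 is still marked as a draft.

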#### 11.3 Sample Size/Accrual Rate

Based upon a previous cross-sectional survey at Columbia University, 253 consecutive breast cancer patients on adjuvant AI therapy were screened over a 4-month period; 47% reported joint pain which started or worsened after initiation of AI therapy and among those with AI-related arthralgias, about two-thirds reported a worst pain score  $\geq 5$  points on a 0-10 scale. Therefore, it is anticipated that up to 20 women screened in the clinic

each month may be eligible for this trial. In addition, the Research Recruitment and Minority Outreach Core at Columbia University will be utilized to target women with breast cancer in the community. Based on this strategy, investigators were able to successfully recruit to other intervention studies for AI-related arthralgias, including acupuncture and supplements such as glucosamine/chondroitin and omega-3 fatty acids. Investigators will also advertise through breast cancer support groups and reach out to colleagues in the community who see breast cancer patients

Accrual is expected to be rapid given the common use of AIs for adjuvant therapy in postmenopausal women with breast cancer. Allowing for 6 months ramp-up and IRB approval time, accrual of 1.5 patients per month for each site would allow completion of the study accrual in approximately 2.5 years. Accrual will be assessed every 6 months after study activation. If monthly average accrual is < 50% 1 year after study activation revision will be considered. For an individual site, if there is no accrual in a 6 month period, the study team will evaluate barriers to accrual. If these changes do not improve accrual, the site will be closed.

- 11.4 A Data and Safety Monitoring Committee will oversee the conduct of the study. The Committee consists of four members from outside of SWOG, 3 SWOG members, 3 non-voting representatives from the National Cancer Institute (NCI), and the Group Statistician (non-voting). The members of this Committee will receive confidential reports every 6 months from the SWOG Statistical Center, and will meet at the Group's bi-annual meetings as necessary. The Committee will be responsible for decisions regarding possible termination and/or early reporting of the study.

## **12.0 DISCIPLINE REVIEW**

There will be no formal discipline review for this study.

## **13.0 REGISTRATION GUIDELINES**

- 13.1 Patients must be registered prior to initiation of study intervention (no more than 5 working days prior to planned start of study intervention).
- 13.2 The individual registering the patient must have completed the appropriate SWOG Registration Worksheet. The completed form must be referred to during the registration but should not be submitted as part of the patient data.

OPEN will also ask additional questions that are not present on the SWOG Registration Worksheet. The individual registering the patient must be prepared to provide answers to the following questions:

- a. Institution CTEP ID
- b. Protocol Number
- c. Registration Step
- d. Treating Investigator
- e. Credit Investigator
- f. Patient Initials
- g. Patient's Date of Birth

- h. Patient SSN (SSN is desired, but optional. Do not enter invalid numbers.)
- i. Country of Residence
- j. ZIP Code
- k. Gender (select one):
  - Female Gender
  - Male Gender
- l. Ethnicity (select one):
  - Hispanic or Latino
  - Not Hispanic or Latino
  - Unknown
- m. Method of Payment (select one):
  - Private Insurance
  - Medicare
  - Medicare and Private Insurance
  - Medicaid
  - Medicaid and Medicare
  - Military or Veterans Sponsored NOS
  - Military Sponsored (Including Champus & Tricare)
  - Veterans Sponsored
  - Self Pay (No Insurance)
  - No Means of Payment (No Insurance)
  - Other
  - Unknown
- n. Race (select all that apply):
  - American Indian or Alaska Native
  - Asian
  - Black or African American
  - Native Hawaiian or other Pacific Islander
  - White
  - Unknown

### 13.3 Registration procedures

- a. All site staff will use OPEN to enroll patients to this study. OPEN is a web-based application and can be accessed at <https://open.ctsu.org>, or from the OPEN tab on the CTSU members' side of the website at <https://www.ctsu.org>, or from the OPEN Patient Registration link on the SWOG CRA Workbench.
- b. Prior to accessing OPEN site staff should verify the following:
  - All eligibility criteria have been met within the protocol stated timeframes. Site staff should refer to Section 5.0 to verify eligibility.
  - All patients have signed an appropriate consent form and HIPAA authorization form (if applicable).
- c. Access requirements for OPEN:
  - Site staff will need to be registered with CTEP and have a valid and active CTEP-IAM account. This is the same account (user ID and password) used for the CTSU members' web site.

- To perform registrations on SWOG protocols you must have an equivalent 'Registrar' role on the SWOG roster. Role assignments are handled through SWOG.

Note: The OPEN system will provide the site with a printable confirmation of registration and treatment information. Please print this confirmation for your records.

- d. Further instructional information is provided on the OPEN tab on the CTSU members' side of the website at <https://www.ctsu.org> or at <https://open.ctsu.org>. For any additional questions contact the CTSU Help Desk at [name] or [[contact]](mailto:[contact]).

13.4 Exceptions to SWOG registration policies will not be permitted.

- a. Patients must meet all eligibility requirements.
- b. Institutions must be identified as approved for registration.
- c. Registrations may not be cancelled.
- d. Late registrations (after initiation of treatment) will not be accepted.

#### 14.0 **DATA SUBMISSION SCHEDULE**

14.1 Data must be submitted according to the protocol requirements for **ALL** patients registered, whether or not assigned treatment is administered, including patients deemed to be ineligible. Patients for whom documentation is inadequate to determine eligibility will generally be deemed ineligible.

14.2 Master forms are included in Section 18.0 and (with the exception of the sample consent form and the Registration Worksheet) must be submitted to the Data Operations Center in Seattle. Data from approved SWOG institutions must be submitted on-line via the Web; see Section 14.3a for details. Exceptions to online data submission are patient-completed (e.g., Quality of Life) forms and source documents (e.g., pathology/operative/lab reports).

